## Abstract

**Background:**

Silent brain infarcts are detected by neuroimaging in up to 20% of asymptomatic patients based on population studies. They are five times more frequent than stroke in general population, and increase significantly both with advancing age and hypertension. Moreover, they are independently associated with the risk of future stroke and cognitive decline.

Despite these numbers and the clinical consequences of silent brain infarcts, their prevalence in Mediterranean populations is not well known and their role as predictors of future cerebrovascular and cardiovascular events in hypertensive remains to be determined.

ISSYS (Investigating Silent Strokes in Hypertensives: a magnetic resonance imaging study) is an observational cross-sectional and longitudinal study aimed to: 1- determine the prevalence of silent cerebrovascular infarcts in a large cohort of 1000 hypertensives and to study their associated factors and 2-to study their relationship with the risk of future stroke and cognitive decline.

**Methods/Design:**

Cohort study in a randomly selected sample of 1000 participants, hypertensive aged 50 to 70 years old, with no history of previous stroke or dementia.

On baseline all participants will undergo a brain MRI to determine the presence of brain infarcts and other cerebrovascular lesions (brain microbleeds, white matter changes and enlarged perivascular spaces) and will be also tested to determine other than brain organ damage (heart-left ventricular hypertrophy, kidney-urine albumin to creatinine ratio, vessels-pulse wave velocity, ankle brachial index), in order to establish the contribution of other subclinical conditions to the risk of further vascular events. Several sub-studies assessing the role of 24 hour ambulatory BP monitoring and plasma or genetic biomarkers will be performed.

Follow-up will last for at least 3 years, to assess the rate of further stroke/transient ischemic attack, other cardiovascular events and cognitive decline, and their predictors.

**Discussion:**

Improving the knowledge on the frequency and determinants of these lesions in our setting might help in the future to optimize treatments or establish new preventive strategies to minimize clinical and socioeconomic consequences of stroke and cognitive decline.

## Background

Hypertension is the most important modifiable vascular risk factor for stroke and it is commonly widespread in the aging population.

For a long time, treatment for hypertension has been focused on blood pressure (BP) levels as the main measure to determine the need and type of treatment. This approach has changed over the past years, emphasizing that diagnosis and treatment should be based on the quantification of global cardiovascular risk. According to the European guidelines on hypertension [1], common variables used to stratify risk are based on the presence of vascular risk factors (family history of premature cardiovascular disease, smoking habits, glucose and lipid parameters) plus further identification of clinical or subclinical target organ damage. Hypertension-related disease in several organs might indicate progression and markedly increase the risk beyond that caused by the BP levels or risk factors presence.

Since evidences advise for different goals of treatment in high risk individuals as compared with lower risk hypertensives [1], whenever possible, it is recommended to measure target organ damage in different tissues (i.e. heart, blood vessels, kidney and brain) because multiorgan damage is associated with worse prognosis [2]. Many different markers have been already described, such as electrocardiographic/echocardiographic markers, intima media thickness, pulse wave velocity as a marker of arterial stiffness or markers of endothelial dysfunction, among others, that can be useful identifying target organ damage. The main limitations are of course, costs and availability of diagnostic procedures and particularly for subclinical conditions, there is still limited knowledge on their predictive capacity for risk evaluation.

Regarding brain as hypertension target organ, subclinical or “silent” vascular brain lesions (i.e. infarcts, microbleeds, white matter changes) are often detected by neuroimaging in asymptomatic patients. Specifically, silent brain infarcts are five times more frequent than stroke in general population, and increase significantly both with advancing age and hypertension [3]. The term “silent” might not be entirely appropriate since these lesions could be often associated with unnoticed or subtle symptoms in patients that never asked for an evaluation, making impossible a diagnosis of stroke. The prognosis associated with these “silent” infarcts is not favourable at all, and their presence independently predicts further stroke and cognitive decline [4,5]. For all these reasons, silent brain infarcts have been recently included in the AHA Updated definition of stroke, thus emphasizing their clinical relevance [6]. This will have important consequences in public health, as it is expected to largely increase stroke prevalence. Moreover, their detection might have the potential to improve the selection of patients at higher risk for future stroke and cardiovascular events, who might benefit from more aggressive preventive treatments.

Hypertension has been related not only to the presence of silent vascular brain lesions but to the appearance of new lesions on follow-up, which can occur in up to 40%, considering progression of white matter changes [7]. Interestingly, this effect on progression is much more relevant at younger or midlife patients than later on [7,8]. Therefore, preventive strategies should pay much more attention to younger subjects, who are likely to have long term exposure to an increased risk in the following years [1].

Studies focusing on hypertensive participants have been performed, and reported a prevalence of silent brain infarcts that ranges from 20 to 86% of subjects aged 40 to 88 years old. Of note, most of these studies have included mainly Japanese populations, whereas data on Mediterranean Caucasian populations is still limited [7].

With this background, the ISSYS is designed as a cross-sectional and longitudinal study aimed to: (1) investigate the prevalence of silent cerebrovascular lesions, as signatures of brain organ damage, in a cohort of middle and advanced aged (50–70 years old) caucasian Mediterranian hypertensives and (2) to study their relationship with the risk of future stroke and cognitive decline.

## Methods/Design

ISSYS (Investigating Silent Strokes in Hypertensives: a magnetic resonance imaging study) is an observational cross-sectional and longitudinal study aimed to determine the prevalence of silent cerebrovascular lesions in a large cohort of hypertensives and to study their associated factors.

On baseline all participants will be also tested to determine other than brain (vascular, kidney, heart) organ damage, in order to establish the contribution of other subclinical conditions to global vascular risk.

Follow-up is planned to last for at least 3 years, to assess the rate of further Stroke/TIA and cardiovascular events as well as cognitive impairment, and their predictors.

### Subject selection

The basic design of ISSYS is a cohort study among 87000 persons aged 50 to 70 years old and living in the district of the north metropolitan area of Barcelona (SAP Muntanya). This site was chosen for several reasons. First, in the Primary Healthcare system there is a computer-based registry for all patients in this area who mainly attend these services rather than other private options. Second, the study is coordinated between the Primary HealthCare services in this area and the researchers from Research Institute and Vall d’Hebron Hospital, which is the public health tertiary reference centre for this area.

The study is carried out in patients diagnosed of essential hypertension who are routinely attended by general practitioners. According to the registry, around 27000 participants could be eligible for the study, since they are hypertensives and stroke-free and have been randomized after stratification by age, gender and prevalence of hypertension covering all the area.

After randomization, patients have been invited by phone to participate in the study and scheduled for a baseline evaluation at their own Primary Care centre.

Estimated sample size will be 1000 participants, who will be enrolled during 18 months and then participants will be followed-up, for at least three years.

The study protocol has been approved by the Ethics Committee of Vall d’Hebron Hospital and IDIAP Jordi Gol (University Research Institute in Primary Care).

### Baseline visit and procedures

#### Inclusion and exclusion criteria

At inclusion visit, fulfilment of inclusion and exclusion criteria is re-assessed by investigators. Briefly, inclusion criteria consists on: 1)Patients with essential hypertension diagnosed at least one year earlier; 2) Age comprised between 50 and 70 years; 3) Patients who give their consent to participate in the study.

Patients are excluded when: 1) they have history of previous stroke or dementia; 2) Brain MRI is contraindicated; 3) there is a suspicion of white coat hypertension syndrome or 4) patients affected by a terminal illness preventing future follow-up examinations, based on the investigator criteria.

A particular effort is made to rule out the presence of a previous stroke, and for that purpose investigators are trained and an adaptation of the Stroke Symptom Questionnaire by Berger K and collaborators is used [9].

Likewise, when a suspicion of dementia appears, following DSM-IV-R criteria [10] the patient is not included in the study and a proper evaluation in the presence of a caregiver is therefore recommended.

#### Clinical data collection

All procedures for baseline and follow-up visits are summarized in Figure 1.

**Figure 1 F1:**
[figure not shown]
ISSYS procedures and outcomes for baseline and follow-up visits.

After inclusion, the participant is asked about demographical and personal medical history. Briefly, demographical information includes age, gender, ethnicity, current or former occupation, and the maximum educational level (or completed years of schooling) achieved by the patient.

Regarding medical history, the participant is asked about the duration of hypertension, the presence of other vascular risk factors such as diabetes mellitus, hyperlipidemia, alcohol intake (grams per week), smoking habit (current, former, never) and family history of premature vascular disease and dementia in first grade relatives.

Also a directed questioning is performed to assess for the existence of an established cardiovascular, kidney or systemic disease, together with the history of retinal abnormalities or the presence of a sleep apnea syndrome. Global vascular risk is calculated applying the SCORE risk charts and Framingham-calibrated REGICOR function when appropriate [11,12].

Data concerning ambulatory and home blood pressure, home medication and treatment adherence is collected. To evaluate treatment adherence, the validated questionnaire published by Morisky and collaborators [13] is used. Briefly, this scale was developed to assess treatment compliance in hypertension and currently is used in many other chronic conditions. It consists in 4 questions, with yes/no answers which should be asked along the clinical interview, and reflect the patient’s attitude towards treatment. It is useful to find out whether or not the patient is a good complier and the causes for non-adherence.

Finally, the clinical interview ends with two self-administered questionnaires assessing life-style habits (physical activity and diet). Physical activity is evaluated by means of the International Physical Activity Questionnaire (IPAQ) [14] and dietetic habits are evaluated with a short questionnaire on frequency of dietary intake [15].

#### Physical examination and vascular testing

Regarding physical examination, some measures are taken and recorded such as height, weight, waist circumference and BP (mean of the last two out of three measurements after five minutes rest).

Plus, a standard 12-lead ECG is performed to assess for signs of left ventricular hypertrophy (single measurement of R wave in aVL [16]) and heart rhythm disorders.

Afterwards, vascular testing is performed with the Vicorder™ device (Skidmore Medical Ltd, Bristol, UK). The Vicorder™ is small, portable, non-invasive and non-operator dependent device suited for use in community based studies [17]. This system provides two BP measurement channels and two Photoplethysmography (PPG) channels for the measurement of blood flow.

Briefly, two measurements are taken for each patient: carotid-femoral pulse wave velocity (cf-PWV) and the ankle-brachial index (ABI).

Cf-PWV is measured as the best approximation of aortic pulse wave velocity (aPWV), a marker of arterial stiffness. For the measurement, the patient should be resting in a supine position, with the head and shoulders raised by about 30 degrees allowing venous return from the brain and avoiding signal contamination by the Jugular vein. A neck-pad should be placed at the lower centre part of the Right Common Carotid Artery as tightened as possible without discomforting the patient. A distal BP cuff should be located on the ipsilateral upper thigh, as high to the groin as possible. The neck-pad and thigh cuff are inflated by the Vicorder to 60 mmHg and then deflated to obtain a pressure tracing. Cf-PWV is calculated by the Vicorder by comparing carotid and femoral pressure tracings after a stable pattern is obtained. Then, cf-PWV is defined as the ratio of the distance between the carotid and the thigh position and the time it takes for the pulse wave to travel from the proximal to the distal locations. For anatomical reasons, the distance between suprasternal notch and the centre of femoral cuff is chosen as the best estimation of the distance between the two arterial sites.

ABI is measured according to the current guidelines of the American Heart Association for each side as the ratio of the highest systolic BP of each ankle and the highest systolic BP of both upper limbs [18]. The lowest of the right and left ABI values will be used.

In this case, systolic BP is determined by PPG, and as it has been previously described [19]. PPG is a fast and accurate technique and can be considered a good alternative to Doppler ABI measurement. Both sides can be examined simultaneously. Briefly, a cuff is placed around the limb of interest and a PPG signal is obtained distal to the cuff. Then, the cuff is inflated to a pre-defined target pressure and afterwards the cuff will automatically bleed pressure and the PPG signal reappears when the systolic BP is reached.

#### Cognitive assessment

On baseline, all patients will be evaluated by means of the Dementia Rating Scale-2 developed by Mattis, which is a screening tool for dementia and mild cognitive impairment. Our complete cognitive assessment protocol on baseline and follow-up has been published in detail previously [20].

#### Laboratory testing

A blood sample will be drawn after overnight fast where the basic hematology (hemoglobine, leukocyte and platelet count) and biochemistry profile (glucose, total cholesterol, creatinine, sodium, potassium and liver function) are determined. Also, plasma and serum will be obtained on baseline visit after 15 minutes centrifugation (3500 rpm) and frozen at -80°C for future biomarker determination. DNA and RNA will be also obtained and stored for further studies.

Finally, a urine sample will be collected and sent to central laboratory for albumin to creatinine ratio (UACR) determination.

#### Neuroimaging protocol

A brain MRI with a pre-stablish data acquisition protocol (Table 1) will be performed within the next month after study entry. All examinations will be performed with the same 1.5 Tesla MR (Signa HDx 1.5, General Electrics, Waukeska, WI). MR will include axial and sagittal T1 weighted images. Midline sagittal images will be used to identify the anterior-posterior commissure line, along which all oblique axial images are aligned. Also, Axial Propeller T2-weighted images, axial fluid-attenuated inversion recovery (FLAIR) and axial GRE images will be obtained. Images will be displayed on workstations monitors to be evaluated by trained readers blinded to patients’ characteristics. All images will be primarily assessed by two neuroradiologists and in a second term by the same readers plus an experienced stroke neurologist. Intra and inter-reader concordance will be provided for all lesions of interest and disagreements in assessment will be solved by consensus.

**Table 1 T1:** MRI parameters in the ISSYS

**Sequence**	**Mode**	**Time**	**TR/TE**	**TI**	**Number of slices**	**Slice thickness/gap (mm)**	**FOV**	**Matrix**
Localizer	3D							
SE SAG T1-w	2D	3:06	400/10		20	5/1.5	256	256x224
SE AX T1-w	2D	2:58	520/10		24	5/1.0	256	256x224
Propeller AX T2-w	2D	2:40	5500/125		20	5/1.5	256	448
AX FLAIR	2D	3:20	10000/120	2200	20	5/1.5	256	320x192
AX GRE	2D	1:55	675/18		20	5/1.5	256	288x224

*SE* Spin Echo, *SAG* Sagital, *AX* Axial, *Propeller* Periodically Rotated Overlapping Parallel Lines with Enhanced Reconstruction, *FLAIR* Fluid Liquid Attenuated Inversion Recovery, *GRE* Gradient Echo, *TR* Repetition Time, *TE* Echo Time, *FOV* field of view, Matrix (Frequency x Phase).

Silent brain infarcts will be defined as previously [21] as lesions of ≥ 3 mm in diameter in their widest dimension, with cerebrospinal fluid signal characteristics in all pulse sequences, and with a hyperintense rim surrounding the lesion in FLAIR images. A particular effort will be made to differentiate these cavitated lacunes from large dilated perivascular spaces for lesions >3 mm, based on location criteria. Lesions located in areas with high prevalence of enlarged perivascular spaces, such as the lower third of basal ganglia will not be considered as infarcts. Anatomical localization for infarcts will be recorded as cortical, subcortical, basal ganglia, brainstem and cerebellum and number of lesions will be counted in case of multiple lesions.

An additional analysis will be performed for lacunar infarcts, defined as those of minimum 3 mm diameter and maximum 20 mm, located at the basal ganglia, internal capsules, thalamus, deep cerebral white matter and brainstem. An infarct located in the cortex, even if it reaches the subcortex will be recorded as cortical.

White matter hyperintensities will be rated according to the Age-related white matter changes (ARWMC) scale developed by Wahlund and col [22] that assesses presence and severity of white matter changes in the frontal, parietooccipital, temporal, basal ganglia and infratentorial areas separately in each hemisphere, ranging from 0 to 30 points.

Enlarged perivascular spaces (EPVs) or Virchow-Robin spaces will be defined as small (<3 mm), sharply delineated structures of cerebrospinal fluid (CSF) intensity following the course of perforating vessels and will be rated in T2-weighted images at the centrum semiovale, basal ganglia and midbrain following the scale reported by Doubal and collaborators [23]. Briefly, for basal ganglia and centrum semiovale, the rating will be as follows: 0: Absent; 1: Mild (from 1 to 10 EPVs); 2: Moderate (from 11 to 20 EPVs); 3: Frequent (from 21 to 40 EPVs); 4: Severe (more than 40 EPVs). For midbrain a rating of 0 will be considered when no EPVs is visible, and a rating of 1 when they are visible. For rating purposes, both hemispheres will be considered separately and the highest score of them will be chosen.

The presence of brain microbleeds, together with their number and location will be recorded following the Brain Observer Microbleed Scale (BOMBS) scale developed by Cordonnier and collaborators [24].

Representative MRI images for the lesions of interest are shown at Figure 2.

**Figure 2 F2:**
[figure not shown]
**Representative examples of subclinical/silent cerebrovascular lesions.** From left to right: Brain infarct affecting caudate nuclei (FLAIR MRI), brain microbleed in left thalamus (GRE MRI), enlarged perivascular spaces involving basal ganglia (T2 MRI) and extensive white matter changes (FLAIR MRI).

### Follow-up visits

The participants will be contacted yearly by phone, one and two years after the inclusion visit. They will be asked about BP control, appearance of new vascular risk factors, and the presence of stroke/TIA or new vascular events. In case of any event has occurred, this will be verified by checking clinical records from their family doctors and hospital records. Participants will also be asked about medical treatment adherence using the same questionnaire performed at baseline and treatment adverse events.

Finally, three years after inclusion a new visit is planned by the investigator’s team at the primary care center where the patient belongs, when data relative to new medical history and physical examination (blood pressure, height and weight and waist circumference measurement) will be collected, together with a new cognitive assessment with the Dementia Rating Scale-2.

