#### Preventive treatments during follow-up

After baseline visit is completed and MRI is performed, primary care physicians will receive a summary with the most relevant results for each participant. Family doctors will take care of vascular risk factor control, following their routine practice. As for silent brain infarcts, since at present there is no clear evidence of whether a secondary stroke prevention should be applied to these patients and until new information comes from randomized clinical trials, recommendations will be to optimize BP control in all cases as much as possible and considering start antiplatelet treatment and/or cholesterol-lowering drugs in cases with the estimated global vascular risk is high (≥10 score in the Framingham-calibrated REGICOR function) [1].

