### Study outcome

The primary outcomes of this study are the determination of the prevalence of silent brain infarctions and other silent lesions (as described in the neuroimaging protocol) and the presence and time to first-ever stroke (fatal or non-fatal ischemic or hemorrhagic stroke) or TIA. Stroke will be defined clinically as a focal neurological deficit thought of vascular origin, lasting more than 24 hours and confirmed by clinical evaluation and the use of a brain CT scan or MRI. TIA will be defined according to the classical definition, as an acute focal neurologic deficit due to cerebral ischemia that resolves completely within 24 hours, regardless of neuroimaging findings.

Other cardiovascular events will be analysed as secondary events: coronary events (myocardial infarction, angina requiring hospitalization, coronary angioplasty or surgery); cardiac failure requiring admission to hospital; vascular complications (lower limbs, aorta or carotid arteries) requiring revascularization and vascular death.

Finally, cognitive decline will be evaluated as secondary end-point during follow-up.

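### Recording of TIA in the primary longitudinal outcome can depend on the baseline MRI result, because events are verified partly from records of physicians who receive a summary of that baseline

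*Protocol article*

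**What the plan says.** All references are to the protocol article.

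- **Finding events (Follow-up visits).** "The participants will be contacted yearly by phone, one and two years after the inclusion visit", with a visit at three years. For any event reported, "this will be verified by checking clinical records from their family doctors and hospital records".
- **Disclosure (Preventive treatments during follow-up).** Once the baseline visit and MRI are done, "primary care physicians will receive a summary with the most relevant results for each participant". The same paragraph turns to infarcts: "As for silent brain infarcts, since at present there is no clear evidence of whether a secondary stroke prevention should be applied to these patients". Recommendations to the physicians follow.
- **Outcome (Study outcome).** Time to first stroke or TIA is a primary outcome. Stroke is a focal deficit "lasting more than 24 hours and confirmed by clinical evaluation and the use of a brain CT scan or MRI". TIA is defined "as an acute focal neurologic deficit due to cerebral ischemia that resolves completely within 24 hours, regardless of neuroimaging findings".
- **Blinding (Neuroimaging protocol).** Images are "to be evaluated by trained readers blinded to" patient characteristics. This is the only blinding that the article describes.
- **Analysis (Statistical methods).** Predictors of stroke/TIA are examined by multivariable Cox regression and reported as hazard ratios with 95% confidence intervals. The second aim (Background) is the relation of silent lesions to later stroke and cognitive decline.

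**The concern.** In a cohort study the outcome should be found and classified in the same way whether or not the exposure is present. Here the exposure is a silent infarct on the baseline MRI. One of the two sources used to verify the outcome is written by physicians who have been sent the main baseline results.

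A physician who knows of an infarct may be readier to call a transient deficit a TIA, to refer it, or simply to note it. TIA is the component most open to this, since its definition rests on transient symptoms and needs no imaging. Blinding the MRI readers protects the classification of the exposure but does nothing for the outcome.

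At stake is the hazard ratio that answers the second aim. Covariate adjustment in the Cox model cannot remove an error in the outcome that depends on the exposure itself.

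**Working it through.** **1. The chain, link by link**

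| Link | Status in the article |
|---|---|
| Family doctors receive a summary of the main baseline results | Stated |
| The summary includes silent infarcts | Strong inference from the infarct-specific advice in the same paragraph |
| Events are verified in family-doctor and hospital records | Stated |
| TIA is in the primary outcome and needs no imaging | Stated |
| Stroke needs clinical evaluation plus CT or MRI | Stated |
| Those who classify events know the MRI result | Not stated either way |

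The mechanism needs only the first four links. It works through what informed physicians write, so it does not depend on who classifies the events.

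**2. The plan's own figure**

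Statistical methods expects a prevalence of 10% and asks for ±2% with 95% confidence:

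n = 1.96² × 0.10 × 0.90 / 0.02² = 864.3, rounded up to 865.

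This matches the stated 865, later raised to 1000. It concerns prevalence only and is untouched by this point. It does give the split used in step 4: 10% of 1000 is about 100 carriers and 900 non-carriers.

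**3. Effect of differential labelling on the hazard ratio**

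Let s be the share of TIA among events in non-carriers. Let f be the ratio of TIA recording, carriers to non-carriers, that is due to labelling alone. With no true association:

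observed HR = (1 − s) + s × f

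The article gives neither s nor f, so both are assumptions.

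| s | f = 1 | f = 1.5 | f = 2 |
|---|---|---|---|
| 0.20 | 1.00 | 0.80 + 0.30 = 1.10 | 0.80 + 0.40 = 1.20 |
| 0.35 | 1.00 | 0.65 + 0.525 = 1.175 | 0.65 + 0.70 = 1.35 |
| 0.50 | 1.00 | 0.50 + 0.75 = 1.25 | 0.50 + 1.00 = 1.50 |

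If labelling does not differ (f = 1), this route adds no bias. A true hazard ratio other than 1, common to stroke and TIA, is multiplied by the same factor.

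**4. The same in counts**

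The article gives no event rate. Assume a three-year risk of 2%, 3% or 4.5% in both groups. The 100 carriers would then have 2, 3 or 4.5 expected events.

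- One extra recorded TIA among carriers gives a crude ratio of 3/2 = 1.50, 4/3 = 1.33 or 5.5/4.5 = 1.22.
- Two extra give 4/2 = 2.00, 5/3 = 1.67 or 6.5/4.5 = 1.44.

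With so few expected events among carriers, one or two labels can move the estimate visibly.

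**5. What a stroke-only analysis can carry**

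Assume a 3% risk in non-carriers, a true hazard ratio of 2 and a TIA share of 33%. Events are 900 × 0.03 + 100 × 0.06 = 33, of which 0.67 × 33 ≈ 22 are strokes. By Schoenfeld's approximation with 10% exposed, power is Φ(√(d × 0.09) × ln 2 − 1.96) for d events. This is about 22% for stroke/TIA (d = 33) and 16% for stroke alone (d = 22). The stroke-only result is useful as a comparison of estimates, not as a second significance test.

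**The case against.** **The article is condensed, and blinded classification may be set out elsewhere.** This stands, and the absence of such a description is not the point. A reader might infer that those who classify events know the MRI result, but the article does not say so. The point rests on the stated combination of disclosure, record source and TIA definition. A blinded committee would still be reading notes written by informed physicians.

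**Events start from the participant's own report, hospital records are also checked, and stroke needs imaging.** This also stands. It narrows the concern to TIA in the main and leaves stroke less exposed. It does not remove the concern for TIA, where the family doctor's note may be the main evidence.

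**The direction is not settled.** A reader might infer that the hazard ratio must be biased away from 1. The documents do not support that. The same disclosure comes with recommendations on prevention, and treatment prompted in carriers could pull the hazard ratio towards 1. Only the ascertainment route considered alone points upwards.

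**The size is assumed.** Correct. Nothing in the article supports a particular labelling factor, and a factor of 1 is possible.

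**Cognitive decline.** A reader might extend the argument to the three-year Dementia Rating Scale-2, since the investigators' team holds that visit. The article does not support this. Cognitive assessment refers to a separately published protocol, and nothing says that the testers see the MRI data.

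**Redaction comes too late.** Partly true. Removing the MRI result from an extract cannot undo a label or referral already made. For that reason redaction alone is not enough.

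**Conclusion.** The concern holds in a limited form. As written, the plan allows the recording of TIA to depend on known infarct status. Through that mechanism the hazard ratio of silent infarct for stroke/TIA can be inflated, and the Cox model cannot correct it. Stroke confirmed by imaging is less affected.

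The article does not allow the size to be computed. Under no true association, the observed hazard ratio is 1.0 with equal labelling and 1.10 to 1.50 for an assumed TIA share of 20–50% and labelling factor of 1.5–2. The conclusion also rests on the strong inference that the summary sent to physicians includes infarcts. The net bias, once preventive treatment is allowed for, could go either way. The prevalence aim and the 865/1000 sample size are unaffected.

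**What to change.** 1. **Follow-up visits.** State that existing study staff classify each reported stroke or TIA against the definitions in Study outcome, working from a record extract with the baseline MRI result removed.
2. **Statistical methods.** Add a Cox analysis of stroke alone (deficit lasting more than 24 hours, confirmed by CT or MRI) as a sensitivity analysis beside stroke/TIA. Compare the two estimates and their intervals without requiring both to be significant. With few events, a rule that both be significant could block a true association. Interpret with caution a stroke/TIA association that is not seen in direction and size for stroke alone.

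Neither change alters what physicians are sent or how participants are managed.

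**Cost.** Redaction of a small number of event files, which is a modest added step, and a wider interval for stroke alone. Redaction reduces the influence of the MRI result on final classification. It does not reach labelling or referral that has already happened, so the stroke-only analysis is needed to show whether that matters.
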